## **4. Detailed research description & Work Plan**

### **Introduction: IOTA Phase 3**

The work Plan is entirely focused to IOTA Phase 3 data collection and validation of the complete diagnostic algorithm. The aim of IOTA Phase 3 is to incorporate the IOTA mathematical models that predict the character of an adnexal mass in daily clinical practice using centre-specific cut-offs and to evaluate second stage tests in patients with adnexal masses that are difficult to classify in order to obtain more reliable results. For clarity of exposition we repeat here the objectives.

### **The objective of IOTA Phase 3**

The main objective of this project is to improve preoperative diagnosis and subsequent management of patients with adnexal tumours by advanced algorithms in order to decrease morbidity and costs and in order to improve survival of patients with ovarian cancer. In particular, we aim to validate the added value of mathematical models as a new diagnostic tool in the prediction of ovarian cancer in clinical practice. First of all, we aim to prove their enhanced diagnostic performance and generalized applicability as a first stage examination. In cases where

prediction is unreliable, we aim to further improve the predictive performance of this diagnostic tool with second stage tests.

To achieve these objectives the project is divided in work packages each having its own sub-objective.

WP1: Prospective external validation of predictive mathematical models and pattern recognition to distinguish between malignant and benign adnexal masses

WP2: Validation of intravenous ultrasound contrast agents: quantitative analysis of contrast uptake and washout in tumor

WP3: Validation of proteomic analysis

WP4: Validation of a new set of tumour markers

WP5: Validation of 3D power Doppler

WP6: Validation of a new model, based on grey scale ultrasound and colour Doppler information, specifically designed for “difficult” tumours

The Work Plan now describes each of these Work Packages and details how each objective is achieved. The link between the different work packages is made clear in the schematic representation of the diagnostic algorithm. Realisation of the work plan should result in optimising all parameters of this diagnostic scheme with respect to diagnostic performance.

### **Work package 1:**

**Objective 1: Prospective external validation of predictive mathematical models and pattern recognition to distinguish between malignant and benign adnexal masses**

The aim of this work package is to validate the IOTA mathematical models that predict the character of an adnexal mass in daily clinical practice using centre-specific cut-offs and to select those patients that are difficult to classify or to diagnose (i.e. with uncertain subjective assessment or uncertain predictive value) for a second stage examination. This work package is further subdivided in 6 tasks.

#### **Task 1.1: Study protocol**

The detailed study protocol for IOTA Phase 3 will be approved by the IOTA Steering Committee and then submitted to all relevant Ethical Committees for clinical studies.

Patients will give informed consent prior to participate in this study. Blood samples are only taken after obtaining written informed consent from each patient.

#### **Task 1.2: Data collection and management**

For the data collection of IOTA phase 1 and IOTA phase 2, a dedicated, secure data collection system was developed. A unique identifier was generated automatically for each patient's record based on the identifier for the centre, the patient's birthday and the date of the ultrasound scan. Clinicians at each centre could only view or update patients records from their own centre. In IOTA phase 1, the data collection was performed web-based, the investigators needed to login and to complete online a case report form. Data security was ensured by not recording the patient's name and by encrypting all data communication using a 54-bit SSL (Secure Socket Layer) certificate. For IOTA phase 2, an Astraia software application has been developed ([www.astraia.com](http://www.astraia.com)) which enables the researchers to complete the data offline in an electronical case report form. And afterwards, they transferred it to a central database located in Belgium. Since this second method was approved much more user-friendly by the clinicians, the data collection of IOTA phase 3 will be similarly executed.

Each participating centre inserts the clinical and ultrasound data in a specifically designed Astraia study screen. No missings are allowed during data submission, except for the CA-125 marker. A subjective assessment whether the tumour seems benign or malignant as well as the degree of certainty is given by the ultrasound examiner and this assessment is frozen in the local Astraia database before the results of the mathematical model become available to the examiner.

### VARIABLES needed to test mathematical models in IOTA PHASE 3

| Variable                          | Acronym        | LR | BMLP | BPER | LS-SVM/
RVM | MC1 | MC2 |
|-----------------------------------|----------------|----|------|------|----------------|-----|-----|
| Personal history of ov. cancer    | Pershistovca   | X  | X    | X    | X              | X   | X   |
| Current use of hormonal therapy   | Hormtherapy    | X  | X    |      | X              |     |     |
| Age                               | Age            | X  | X    | X    | X              | X   | X   |
| Diameters of the lesion           | LesD1-3        | X  | X    | X    |                | X   | X   |
| Pain during examination           | Pain           | X  | X    |      |                |     |     |
| Ascites                           | Ascites        | X  | X    | X    | X              | X   | X   |
| Blood flow within papillary proj. | Papflow        | X  | X    | X    | X              | X   | X   |
| Locularity                        | Locularity     | X  | X    | X    | X              | X   | X   |
| Diameters of solid component      | SolidD1-3      | X  | X    | X    | X              | X   | X   |
| Irregular internal cyst walls     | Wallregularity | X  | X    | X    | X              | X   | X   |
| Acoustic shadows                  | Shadows        | X  | X    | X    | X              |     | X   |
| Color Doppler score               | Colscore       | X  | X    | X    | X              |     |     |
| Number of papillary projections   | Papnr          |    | X    |      |                |     | X   |
| Diameters of the ovary            | OvD1-3         |    |      |      | X              |     |     |
| Bilateral tumors                  | Bilateral      |    |      |      |                | X   | X   |
| Suspected origin (ovary vs other) | Origin         |    |      |      | X              |     |     |

LR (logistic regression):

LR1

LR2

objLR

regLR

BMLP (Bayesian multi-layer perceptron):

BMLP11-2a

BMLP11-2b

BPER (Bayesian perceptron):

BPER11

LS-SVM/RVM (Bayesian least squares support vector machines/relevance vector machines):

BLSSVMlin (using linear kernel)

BLSSVMrbf (using radial basis function kernel)

BLSSVMaddrbf (using additive RBF kernel)

RVMlin

RVMrbf

RVMaddrbf

MC1 and MC2 (Multi-class models):

MLR (multi-category logistic regression)

LR-PC (binary LR models combined using pairwise coupling)

LR-PC2 (similar, but different inputs)

BLSSVM-PC (binary Bayesian LS-SVMs + PC)

KLR-PC (binary kernel logistic regression models + PC)

MKLR (multi-class KLR)

The data are stored locally and by clicking “send data from FTP” all data are automatically and anonymously transferred to the central server in Leuven, where the datamanager checks them.

### **Task 1.3: Data quality checks and storage**

In Leuven a full protocol has been developed for quality checks: 1) cross checks, e.g. in multilocular cysts you may not find papillary structures and 2) manual verification of the outliers. This protocol has already successfully been applied to the data of IOTA phase 1 and 2.

Once the data has passed all quality checks, it is stored in the central database.

### **Task 1.4: Prospective external model validation**

Once the data have been collected, all models of IOTA phase 1 and 2 (i.e. logistic regression models, scoring systems, neural networks, support and relevance vector machines) will be validated prospectively. The AUC, sensitivity, specificity, positive and negative predictive values will be computed.

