### 10. Statistical analysis

New mathematical models have been constructed in IOTA phase 1 and 2. In phase 3 these models will prospectively be evaluated in terms of sensitivity and specificity and overall accuracy (i.e. the proportion of the sum of true positives and true negatives over the total number of cases). Independent risk factors for malignancy will be expressed as odds. The models will be compared by constructing receiver operating characteristic (ROC) curves.

In addition new models based on new variables will be constructed. The data will be thoroughly inspected using univariate analyses (contingency tables and basic descriptive statistics) and multivariate analyses (principal component analysis, biplots, scattermatrices, canonical correlation analysis and logistic regression) to explore the data and to detect multicollinearity and outliers. Manual checks of any outliers will be performed to eliminate mistakes that had occurred during submission of the data.

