#### **State of the art in the consortium and comparative advantage**

#### **O1: Prospective external validation of predictive mathematical models and pattern recognition to distinguish between malignant and benign adnexal masses**

**IOTA phase 1.** During IOTA phase 1 we collected more than 50 ultrasound, demographic and clinical variables of 1,066 patients with an adnexal mass. A histopathologic diagnosis was available for all patients. Patients were collected in 9 different international centres where the ultrasound examination was performed by one of the IOTA expert sonologists following a standardised protocol. In this way we obtained a large and multicentre database that is more likely to resemble the general population [44].

Based on this dataset 12 mathematical models were developed (2 logistic regression models [44], 1 scoring system (unpublished data), 3 neural networks [46] and 6 kernel based models [47] (3 support vector machine models (SVM) and 3 relevance vector machine models (RVM)). On the test set of IOTA phase 1 all models obtained an area under the ROC curve (AUC) of more than 0.92.

**IOTA phase 1b.** In IOTA phase 1b a new dataset of 507 new patients was prospectively collected in 3 of the 9 IOTA centres. All models proved to perform excellent with again AUCs of more than 0.94 (unpublished data).

**IOTA phase 2.** The aim of IOTA phase 2 was to test the IOTA models in new centres with different population characteristics and different levels of ultrasound experience. More than 2,000 patients have been included in 20 centres throughout the world. In a preliminary analysis the main logistic regression model (1) was tested and in every centre the AUC was above 0.87. When tested on the whole dataset the AUC was above 0.93. In IOTA phase 1 and 2 we found that both for the expert sonologist using pattern recognition (subjective impression) as for the mathematical models, approximately 8% of the adnexal masses were difficult to classify as benign or malignant and lied close to the decision boundary. Models that were built especially for the classification of these difficult masses showed disappointing results [45].

**IOTA phase 3 .** During IOTA phase 3, the same centres that participated in IOTA phase 2 will prospectively include a new dataset of more than 2,000 patients but will now be able to evaluate the prediction of the main logistic regression model immediately after performing the ultrasound scan.

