### **Task 1.5: Patient selection for Second stage tests**

The IOTA 2 dataset enables us to describe the population characteristics of each centre in correlation with the performance of the models in that centre. This gives us the opportunity to define centre-specific cut-offs above which an adnexal mass is classified as malignant. Whenever the probability of malignancy is amongst the 15% that lies close to the decision boundary of LR1, the examiner will be obliged to perform one of the second stage tests. In this way, we expect that the adnexal masses of approximately 300 patients will be classified as “difficult” and will need a second stage test.

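### The listed validation measures cover ranking and cut-off accuracy but not calibration, although the plan uses LR1's predicted probability and per-centre cut-offs

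*Protocol*

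**What the plan says.** The Protocol names its performance measures in two places. Task 1.4, which covers all models from phases 1 and 2, says "The AUC, sensitivity, specificity, positive and negative predictive values will be computed". Section 10 (Statistical analysis) says "In phase 3 these models will prospectively be evaluated in terms of sensitivity and specificity and overall accuracy", and then "The models will be compared by constructing receiver operating characteristic (ROC) curves". No part of the document mentions agreement between predicted and observed risk.

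The same document relies on the predicted probability and on where it falls relative to a cut-off:

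- Task 1.5 makes a second-stage test obligatory "Whenever the probability of malignancy is amongst the 15% that lies close to the decision boundary of LR1".
- The introduction to the work plan wants the models brought into practice "using centre-specific cut-offs". Task 1.5 explains that IOTA 2 data will be used to "define centre-specific cut-offs above which an adnexal mass is classified as malignant".
- The consortium section on O1 says that the centres "will now be able to evaluate the prediction of the main logistic regression model immediately after performing the ultrasound scan". Task 1.2 adds that the examiner's own assessment is frozen before the model result appears.

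The study objectives (section 1) also include showing that the models apply generally. No criterion is given for calling a model validated.

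**The concern.** AUC depends only on how the model ranks masses. Sensitivity, specificity and the predictive values depend only on which side of a cut-off each mass falls. None of them asks whether masses given a risk of, say, 10% are malignant about 10% of the time.

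That question matters here because LR1's probability is used directly. It can also go wrong by centre on the Protocol's own account: cut-offs differ between centres because populations and model performance differ. A centre whose patients have systematically higher or lower odds of malignancy than LR1 predicts would show an unchanged AUC. If its cut-off was placed to compensate, the other listed measures would look normal too.

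At stake is whether a validation in 2,000 patients can say that the predicted risks are correct, how much this varies between centres, and how often masses in the LR1 band prove malignant.

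**Working it through.** **The plan's own figure.** Section 3 gives 2,000 patients and Task 1.5 a band of 15%. 0.15 × 2,000 = 300, which matches the roughly 300 difficult masses in Task 1.5. The Protocol gives no other WP1 calculation to reproduce.

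**Inputs from the Protocol.** AUC 0.94 (Background, second phase). Prevalence from the expert-performance counts in the consortium section on O6: 266/1066 = 25.0% and 143/507 = 28.2%; together 409/1573 = 26.0%. About 20 centres (consortium section on O1), so 2,000/20 = 100 patients per centre on average.

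**Assumptions not in the Protocol.** Normal scores with equal variance in benign and malignant masses, a 10% cut-off, and a centre where LR1 doubles or halves the true odds. The 10% serves the arithmetic and is not a proposed cut-off.

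**Model.** The score x is N(0,1) in benign and N(d,1) in malignant masses.

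- AUC = Φ(d/√2), so d = √2 × Φ⁻¹(0.94) = 2.199.
- True log-odds L = ln(0.26/0.74) + d·x − d²/2 = −1.046 + 2.199x − 2.417.
- A 10% cut-off is ln(0.1/0.9) = −2.197 on the log-odds scale.
- If LR1 multiplies the odds by k, its log-odds are L + ln k, and the cut-off falls at L = −2.197 − ln k.
- Specificity = Φ(x at the cut-off); sensitivity = Φ(d − x at the cut-off).

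**Cut-off held at 10%.**

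| | Calibrated (k = 1) | Odds doubled (k = 2) | Odds halved (k = 1/2) |
|---|---|---|---|
| x at the cut-off | 1.266/2.199 = 0.576 | 0.573/2.199 = 0.261 | 1.959/2.199 = 0.891 |
| AUC | 0.94 | 0.94 | 0.94 |
| Sensitivity | 95% | 97% | 90% |
| Specificity | 72% | 60% | 81% |
| PPV | 54% | 46% | 63% |
| Mean predicted risk (observed 26%) | 26% | 32% | 21% |
| Observed/expected | 1.00 | 0.81 | 1.25 |
| Malignant among masses predicted at 5–25% | 12% | 7% | 21% |
| True risk behind a predicted 10% | 10% | 1/19 = 5.3% | 2/11 = 18.2% |

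**Cut-off that follows the centre's shift.** This means 18.2% when the odds are doubled and 5.3% when they are halved. Each mass stays on the same side of the cut-off. Sensitivity (94.8%) and specificity (71.8%) return exactly to the calibrated values, and PPV and NPV with them. The 15% of masses nearest the boundary, measured in log-odds, are also the same masses, with 10.2% malignant in all three cases. Only the predicted risks are wrong, and no listed measure shows it.

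**Range.** With shifts of ±1 in log-odds at prevalence 25%, AUC stays at 0.941 while observed/expected is 0.74 or 1.40. At a fixed 10% cut-off, specificity falls from 0.725 to 0.557, or sensitivity from 0.945 to 0.875. At a fixed 25% cut-off, the falls are 0.864 to 0.740 and 0.865 to 0.741. At prevalence 28% with the 10% cut-off, they are 0.702 to 0.530 and 0.953 to 0.888. A wrong slope also leaves AUC at 0.941: with slope 1.5 at prevalence 25%, observed/expected is only 1.06, but a predicted 10% stands for a true 18.8%. The observed/expected ratio alone is therefore not enough.

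**Precision of a calibration check.** The standard error of the calibration intercept is about 1/√(n × mean of p(1−p)), and the mean of p(1−p) under this model is 0.081. For n = 100 it is 1/√8.1 = 0.35; for n = 2,000 it is 1/√162 = 0.08. In one centre of 100, a doubling of the odds gives 0.693/0.351 = 1.97 standard errors, or about 51% power at the two-sided 5% level. With 50 patients, power is about 29%.

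**The case against.** The strongest reply is that calibration statistics are the sort of detail a statistical analysis plan supplies, and that neither list claims to be complete. The two lists differ: Task 1.4 omits overall accuracy and section 10 omits the predictive values. WP1 also announces six tasks and sets out five. This is fair as far as it goes, and nothing in Task 1.4 is false. But the Protocol describes twice how the models will be validated and names only ranking and classification measures both times. The point is an improvement to a stated method, and nothing in the text suggests that a sixth task would cover calibration.

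Second, the stated use is classification relative to a cut-off, and a centre cut-off that follows the centre's shift leaves the decisions and the 15% band intact. That stands. A reader might infer that miscalibration must send the wrong masses to second-stage testing; the documents do not support this where the cut-off tracks. They do not show that cut-offs derived from IOTA 2 will track in phase 3 either.

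Third, the falls in sensitivity and specificity need a common fixed cut-off, which the Protocol does not plan. That also stands: those figures illustrate a cut-off that fails to track. It would be too strong to say that the listed measures are blind in general, because at a fixed cut-off all but AUC move. What they cannot do is tell miscalibration from a different case mix.

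Two further readings go too far. One is that a miscalibrated model would be declared validated: there is no pass criterion, so it could be, no more. The other is that examiners see a wrong percentage: the text says that the model's prediction or result becomes available, not in what form.

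**Conclusion.** The point holds in limited form. The Protocol validates models that output probabilities, and uses LR1's probability, without listing any check of predicted against observed risk. That AUC misses a log-odds shift is a mathematical fact and needs no assumption; that the other four measures in Task 1.4 miss it when the cut-off tracks follows in the same way. The sizes are illustrative: they rest on the normal-score model, AUC 0.94, prevalence 26%, a fixed 10% cut-off and a doubling or halving of the odds. Under those assumptions specificity falls by 12 percentage points or sensitivity by 5, without the cause being identifiable. The consequence is that the models could be reported as validated while the correctness of their risks remains unexamined. This is a gap in what the validation can conclude. It does not show that LR1 is miscalibrated or that the selection of patients is wrong.

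**What to change.** Extend Task 1.4, and align section 10 with it. For LR1 and every other model that outputs a probability, report the calibration intercept and slope, the observed/expected ratio and a calibration plot. Make the pooled data the primary analysis, and summarise centre-level estimates with a random-effects model. Also report the observed proportion malignant in LR1's 15% band.

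The cost is a little more analysis: it needs only the predicted probabilities and the histology, both already collected. The limitation is precision. With an intercept standard error of about 0.35 at about 100 patients, single-centre results should be read as describing heterogeneity between centres, not as centre-by-centre tests.

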### **Task 1.5: Patient selection for Second stage tests**

The IOTA 2 dataset enables us to describe the population characteristics of each centre in correlation with the performance of the models in that centre. This gives us the opportunity to define centre-specific cut-offs above which an adnexal mass is classified as malignant. Whenever the probability of malignancy is amongst the 15% that lies close to the decision boundary of LR1, the examiner will be obliged to perform one of the second stage tests. In this way, we expect that the adnexal masses of approximately 300 patients will be classified as “difficult” and will need a second stage test.

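### Work package 1 aims at generalised applicability, but the only cut-offs it names are tuned per centre on IOTA 2 data from the same centres, so its threshold-based results alone cannot support that aim

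*Protocol*

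**What the plan says.** The aim and the label are broad. The objective of IOTA Phase 3 states: "we aim to prove their enhanced diagnostic performance and generalized applicability as a first stage examination". Work package 1 carries the title "Prospective external validation of predictive mathematical models and pattern recognition to distinguish between malignant and benign adnexal masses", and the title of Task 1.4 also calls the validation external.

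The method is local. The aim of Work package 1 is to "validate the IOTA mathematical models that predict the character of an adnexal mass in daily clinical practice using centre-specific cut-offs"; the introduction to the work plan says the same in substance. Task 1.5 gives the source of the cut-offs: "The IOTA 2 dataset enables us to describe the population characteristics of each centre in correlation with the performance of the models in that centre". It continues: "This gives us the opportunity to define centre-specific cut-offs above which an adnexal mass is classified as malignant".

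The setting is unchanged from the previous phase. Under the consortium's state of the art (O1, IOTA phase 3), "the same centres that participated in IOTA phase 2 will prospectively include a new dataset of more than 2,000 patients".

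The output is set in Task 1.4: "The AUC, sensitivity, specificity, positive and negative predictive values will be computed". That task names no cut-off. Nowhere does the protocol fix a common cut-off, hold out a centre, or say how a centre without IOTA 2 data would obtain its own cut-off.

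**The concern.** Four of the five measures in Task 1.4 depend on the cut-off. If the cut-off in each centre was chosen from that centre's earlier patients, the results in its new patients describe how local tuning holds up over time. They do not describe a centre that was never tuned, and generalised applicability is a claim about such centres.

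The protocol's own vocabulary supports the distinction. Section 2 (Background) describes Phase 1b, which had new patients in three of the nine original centres, as an internal validation, and reserves the word external for Phase 2. By that usage, cut-offs tuned on IOTA 2 and applied to new patients in IOTA 2 centres are not externally validated.

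At stake is the interpretation of the first-stage result. Published sensitivity and specificity could be read as what any new hospital should expect, when the plan as written does not produce that estimate.

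**Working it through.** **The plan's own figure.** Task 1.5 expects about 300 difficult masses. 15% × 2,000 = 300, so it reproduces and is not in dispute. The point concerns design and interpretation, not arithmetic.

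**Passages side by side.**
- Cut-off: per centre (introduction to the work plan, Work package 1, Task 1.5).
- Data that set it: the centre's own IOTA 2 patients and model performance (Task 1.5).
- Data that test it: new Phase 3 patients in the same centres (consortium section, O1).
- Claim: external validation and generalised applicability (Work package 1, objective of Phase 3).

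The first three together define a temporal validation of the cut-off. The fourth needs evidence from centres that did not set it, or from a cut-off that is the same everywhere.

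**How much data sits behind each cut-off.** The protocol gives three IOTA 2 counts:
- Background: 2,093 / 19 = 110 per centre
- UZ Leuven section: 1,938 / 19 = 102 per centre
- Consortium section, O1: more than 2,000 in 20 centres, so at least 2,000 / 20 = 100 per centre

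The malignant share in IOTA 2 is not given. From the O6 consortium section, IOTA 1 has 266/1,066 = 25.0%, and IOTA 1 and 1b pooled have (266 + 143)/(1,066 + 507) = 409/1,573 = 26.0%. Taking these as assumptions for IOTA 2:
- At 26.0%: 100 × 0.260 = 26.0; 102 × 0.260 = 26.5; 110.2 × 0.260 = 28.6 malignancies per centre.
- At 25.0%: 25.0, 25.5 and 27.5.

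So an average centre tunes on roughly 25 to 29 malignancies. As a gauge of how little that is, an assumed sensitivity of 90% estimated from 26.5 malignancies has a 95% half-width of 1.96 × √(0.9 × 0.1 / 26.5) = 11.4 points. This is the precision of a sensitivity estimate. It is neither the error of a cut-off nor a loss on transfer.

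**What transfer could cost (illustration only).** A binormal simulation used a within-centre AUC of 0.94 (the IOTA 2 value in the Background), 19 centres of 105 patients, 25% malignant, and cut-offs at the Youden optimum. The protocol gives neither the rule for setting cut-offs nor the between-centre shift of the score, so both are assumed. The shift is in within-class SD units. Entries are expected sensitivity / specificity.

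| Shift SD | Own tuned cut-off, new patients, same centre | Common cut-off, new centre | Another centre's tuned cut-off, new centre |
|---|---|---|---|
| 0 | 0.84 / 0.87 | 0.86 / 0.86 | 0.84 / 0.87 |
| 0.25 | 0.84 / 0.87 | 0.85 / 0.86 | 0.83 / 0.86 |
| 0.5 | 0.84 / 0.87 | 0.83 / 0.84 | 0.79 / 0.82 |
| 0.75 | 0.84 / 0.87 | 0.81 / 0.81 | 0.76 / 0.78 |

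The second column, which is what the plan would report, is the same in every row. It therefore carries no information on which row is true. Moving a tuned cut-off to another centre costs nothing at shift 0, and about 8 points of sensitivity (0.840 − 0.759) and 9 of specificity (0.868 − 0.781) at shift 0.75. Tuning noise alone made true sensitivity vary between centres with an SD of about 0.07.

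**The case against.** Several counter-arguments are sound and limit the point.

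- **A reader might infer that sensitivity and specificity do not carry over to other centres.** The documents do not show this. The loss may be nil, and its size depends on heterogeneity that is not reported. What stands is that the planned results cannot show carry-over.
- **A reader might infer that the models cannot be compared on common ground.** That is not so. Section 10 compares them by ROC curves, which need no cut-off, and Task 1.4 reports the AUC.
- **A reader might conclude that external validation is lost altogether.** For Phase 1 models, developed in nine centres, the AUC in the other participating centres is still external. All Phase 3 patients are new, so no patient is used twice.
- **A reader might extend the criticism to the difficult-tumour model in Work package 6.** That package makes no claim of external validation. It is a randomised comparison in new patients, and centre-specific tuning is not described for its model.
- **A common cut-off is not excluded.** Task 1.4 names none, Task 1.5 calls the centre-specific cut-off an opportunity, and the choice of cut-off for a results table is often left to an analysis plan. This has weight. But the introduction to the work plan and Work package 1 both state centre-specific cut-offs as part of the aim, and no other classification cut-off is named.
- **Local thresholds are a legitimate way to bring a model into daily practice.** This also stands, and is why those results should be kept. They answer the question of local implementation, not that of generalisability.

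**Conclusion.** The point holds as one of reporting and interpretation. At cut-offs tuned on each centre's IOTA 2 data, sensitivity, specificity, PPV and NPV in new patients of those centres are a temporal validation. Alone they cannot support the stated aim of generalised applicability, and a centre without IOTA 2 data is given no cut-off at all. Discrimination measured by the AUC is not touched by the tuning.

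The size of any transfer loss cannot be stated from the protocol. The range of zero to 8 or 9 points rests wholly on assumed shifts and an assumed tuning rule. The imprecision of the tuned cut-offs is better grounded: it needs only the reported IOTA 2 counts and a malignant share near that of IOTA 1 and 1b. It rests on average centre size; individual centre sizes are not given.

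**What to change.** In Task 1.4, report sensitivity, specificity, PPV and NPV for each binary model at one common cut-off, the same in all centres and fixed before analysis. Use the development cut-off where one exists. The protocol states none, so where there is none a value should be fixed and recorded in advance. Base the conclusion on generalised applicability on these results, and give the results at centre-specific cut-offs alongside as the local-implementation result.

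Present the AUC and the threshold-based measures separately for centres that did and did not supply data to develop each model, and call the former temporal validation. For a model developed on IOTA 2 data the second group may be small or empty; if so, the report should say so.

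The cost is extra tables from data already collected and a narrower external-validation claim. The change concerns reporting only and leaves the selection of patients for second-stage tests as it is.
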